Aim 1: Determine the clinician-reported feasibility of conducting a clinician-level, randomized controlled trial of TLT compared to usual care in the ED.

Hypothesis: TLT is feasible to conduct a clinical-level randomized study in the ED.

Aim 2: Determine the patient-reported acceptability of TLT in the ED.

Hypothesis: The patients or surrogates (if patients are unable to consent) randomized to TLT will feel more heard and understood about their end-of-life care wishes (primary outcome).

1. **GENERAL DESCRIPTION OF THE STUDY DESIGN**

Overview

To demonstrate the feasibility (Aim 1) and acceptability (Aim 2) of TLT, we will conduct a parallel group, clinician-level, pilot randomized clinical trial among 40 emergency clinicians (~20 in TLT and ~20 in usual care) in the ED.

Randomization: Using REDCap’s integrated randomization module,^24^ we will conduct clinician-level randomization using random blocks of four to ensure that emergency clinicians are evenly distributed one-to-one between intervention and control arms.

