**Aim 2: Patient-Reported Acceptability**

Among the patients who were cared by the emergency clinicians enrolled in the randomized trial, we will measure the patient-reported acceptability of the TLT conversations (intervention arm only) and track their clinical outcomes via electronic health record (EHR) review (both intervention and control arms).

1. **SUBJECT SELECTION**

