**Aim 1:** **Feasibility**

Emergency clinicians are subjects given they will answer few questions (i.e., clinician-reported feasibility questionnaire) after conducting the TLT conversations in the ED. Emergency clinicians will be randomized to intervention (TLT training) vs. usual care (no TLT training).

Inclusion: Attending physicians, resident physicians, or mid-level providers working in the ED who are willing to be randomized to become the study interventionists.

Exclusion: Emergency clinicians unwilling to consent and be randomized to intervention TLT training.

Recruitment: With the Chair’s approval and after reviewing the ED roster, the PI will announce the study in the staff meetings and solicit participation.

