**Aim 2: Patient-reported Acceptability**

The subjects will be seriously ill older adults, or their surrogates being cared for by the participating emergency clinicians (both the intervention or control arms – see details on which outcome to be assessed for which arm in *6 Study Procedures, Outcome Assessment* below). If the emergency clinicians determine that the patient is not able to provide consent due to cognitive impairment, dementia, delirium, or critical illness, the surrogates will participate in the TLT conversations (Table 1).

Inclusion:

a. ≥50 years or older with ≥one serious life-limiting illness* being admitted to intensive care unit in the ED; or

b. ≥75 years or older being admitted to intensive care unit in the ED; or

c. ED clinicians will not be surprised if the patient died in the current hospital admission; and

d. English speaking

*Serious illness criteria with high one-year mortality were selected based on best practice recommendations^25^ similar to prior studies:^26-28^ 1) stage III/IV or metastatic cancer;^29, 30^ 2) end-stage renal disease on dialysis;^31^ 3) chronic heart/lung disease requiring home oxygen supplementation or experiencing shortness of breath with walking;^32, 33^ 4) moderate to severe dementia (surrogate required for enrollment); or 5) ≥2 hospitalizations in the past six months.^29, 34, 35^

Exclusion:

a. Unable or unwilling to provide informed consent; or

b. Non-English speaking; or

c. Clinically inappropriate, determined by emergency clinicians, and no surrogate is available

Recruitment:

| **Table 1. Intervention target and outcome assessment** | | |
| --- | --- | --- |
| **Ability to consent** | **Intervention target** | **Outcome assessment** |
| Present | Patient or surrogate (if patient unwilling due to critical illness) | Patient-reported acceptability + EHR |
| Absent | Surrogate | Surrogate-reported acceptability + EHR |

1. *How individuals are identified for recruitment including description of use of recruitment materials such as flyers, brochures, advertisements, letters, etc.*

🡪 In the ED, we will identify potential subjects by reviewing patients being cared for by the study interventionist clinicians from 8 AM to 10 PM, seven days per week using our EHR. No flyers, brochures, advertisements, or other promotional materials will be used.

🡪 Given the minimal risk of this study, our study team will provide a study information sheet for verbal consent.

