1. *Who is responsible for identifying and recruiting individuals?*

🡪 Upon identification of potential subjects, our research team member (e.g., research assistant) will approach the interventionist emergency clinicians to see if his/her patient can be recruited for this study to confirm the inclusion/exclusion criteria.

1. *When and where individuals are recruited?*

🡪 Potential subjects will be recruited in the ED while receiving care.

🡪 After the intervention emergency clinician completes the TLT conversation, our research team member (e.g., research assistant) will approach the potential subjects or the surrogate for enrollment and completion of the patient-/surrogate-reported acceptability outcomes in the ED.

1. *How recruitment goals match the prevalence rates of the condition/disease being studied and the populations most impacted by the condition/disease being studied?*

🡪 We will recruit from all patients arriving in the ED, which will reflect the prevalence rates of seriously ill older adults in the ED.

1. *Methods to enhance enrollment of diverse individuals and under-represented populations*

🡪 We will cap enrollments of non-Hispanic Whites at 70% of the enrollment target and overenroll other under-represented minorities.

1. **SUBJECT ENROLLMENT**

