**Aim 2: Patient-reported Acceptability**

Pre-screening: We will identify potentially eligible patients using the ED track board in the EHR.

Consent Process:

1. Upon completion of TLT conversation by the interventionist emergency clinician (who also provides clinical care for the patient), our study team (e.g., research assistant, PI) will obtain verbal, informed consent from the patient or surrogate (if applicable) in the ED.
2. The capacity to consent the patient or surrogate is determined by the interventionist emergency clinician who conducted the TLT conversation.
3. **STUDY PROCEDURES**

**Intervention:** Clinician-led conversations about patient’s values and goals, potential benefits and risks of intensive care, and anticipated outcomes are standard of care in the ED. TLT is a multi-modal intervention that provides patient-centered structures to this standard of care. In this evaluation of TLT in the ED, the intervention components will include: 1) a structured conversation guide; 2) clinician training to use the guide; 3) electronic health records (EHR) template for documentation; and 4) standardized communication with the intensivist (**Fig 1**).

1. The TLT Conversation Guide: The structured conversation guide entails discussing patients’ values and goals, prognosis, and shared decision-making to use a trial of intensive care. Originally used in ICU settings,^21, 22^ we systematically refined the guide to be used in the ED incorporating inputs from patient advisors’ and emergency clinicians’ inputs (Appendix).
2. Clinician Training: Leveraging the study team’s expertise in serious illness communication training, the clinician training will include a one-hour didactic on research methodologies and serious illness communication skills, followed by a four-hour communication training with trained actors. Similar training has been described previously.^36-38^
3. EHR Documentation: An Epic template for documenting the TLT conversation findings has been developed (Appendix).
4. **
[figure not shown]
**Intensivist Communication: A standard template to communicate the TLT conversation findings to the intensivists has been developed (Appendix).

Control Group: Emergency clinicians assigned to the control group will not receive the TLT training/guide. Patients cared for by the control group emergency clinicians will receive usual care in the ED. No restrictions will be placed on serious illness conversations in the control group.

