Outcome Assessments: We will collect the following variables during and after the TLT conversations (Table 2).

For Aim 1 Feasibility, we will collect all outcomes from the intervention arm, and EHR outcome from both intervention and control arms.

For Aim 2 Patient-Reported Acceptability, we will collect all outcomes from both the intervention and control arms.

*For clarity, we placed * on outcomes only collected from the intervention arm.*

| **Table 2. Outcomes and Assessment Timing** | | |
| --- | --- | --- |
| **Aim 1: Feasibility (* indicates outcomes collected only from the intervention arm)** | | |
| **Outcomes** | **Descriptions** | **Timing** |
| Time to complete the TLT conversation (primary outcome)* | With direct observation, the study team will record how long it takes to complete the TLT conversation by the intervenist ED clinician. | At the time of TLT conversation |
| Intervention fidelity* | With direct observation, the study team will record the completion of TLT components using an intervention fidelity checklist. | At the time of TLT conversation |
| Clinician-reported feasibility* | The study team will ask the interventionist emergency clinician to complete two 5-point Likert scale questions (i.e., “How feasible was it to conduct the TLT conversation with your patient?” and “How likely would you recommend the TLT conversation for your colleagues?” “Not at all (1)” to “Completely (5)”). | Immediately after the TLT conversation |
| Recruitment* | The percent that agree to conduct TLT conversations | At enrollment |
| Clinician-reported satisfaction* | The study team will ask the interventionist emergency clinician to complete 5-point Likert scale questions (i.e., “How satisfied are you with the conversation? “Not at all (1)” to “Completely (5)”). | Immediately after the TLT conversation |
| EHR documentation by inpatient clinicians (i.e., intensivists) | Review EHR for new documentation of reference to TLT, serious illness conversation, change in code status, or advance directive forms by inpatient clinicians. | After 24 hours, 48 hours, and 1 week |
| **Am 2: Patient-Reported Acceptability (* indicates outcomes collected only from the intervention arm)** | | |
| **Outcomes** | **Descriptions** | **Timing** |

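### Recruitment is written only for intervention clinicians' patients, with consent after a completed TLT conversation; control patients, who must supply both-arm survey outcomes, have no consent step or survey time

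*Protocol*

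**What the plan says.** Randomisation is of clinicians: "we will conduct clinician-level randomization using random blocks of four" (General Description of the Study Design).

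Control-arm patient data are required. Subject Selection, Aim 2, defines the subjects as patients or surrogates cared for by participating clinicians in "both the intervention or control arms". Study Procedures, Outcome Assessments, says for Aim 2 that "we will collect all outcomes from both the intervention and control arms", with an asterisk marking the intervention-only exceptions. In Table 2 only the acceptability item carries the asterisk under Aim 2. Heard and Understood, quality of end-of-life communication, decisional regret and the EHR outcomes do not. The Aim 2 hypothesis in Specific Aims is comparative: patients randomised to TLT are expected to feel more heard and understood.

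The recruitment steps name one arm. Under Subject Selection, Recruitment, "we will identify potential subjects by reviewing patients being cared for by the study interventionist clinicians". The eligibility check is made with the interventionist clinician. Then: "After the intervention emergency clinician completes the TLT conversation, our research team member" makes the approach for enrolment. Subject Enrollment, Consent Process, has the same trigger: "Upon completion of TLT conversation by the interventionist emergency clinician (who also provides clinical care for the patient), our study team" takes verbal consent. Capacity is judged by the clinician who held that conversation.

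The study design section is narrower than Outcome Assessments. There, "we will measure the patient-reported acceptability of the TLT conversations (intervention arm only"), and the only Aim 2 data mentioned for both arms are EHR clinical outcomes.

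**The concern.** Two sets of instructions do not fit together. One requires survey outcomes from control patients. The other gives no means of consenting or surveying them, because the triggering event is the intervention itself.

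A team following the text literally collects no control surveys, and the comparative hypothesis has no comparator. A team that improvises admits control patients by an unstated route at an unstated time, while intervention patients enter only after the conversation has been completed. Completion happens after randomisation and may be related to the outcomes.

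Three things are then at stake:

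- any between-arm estimate from the surveys due in both arms;
- the comparison of patient demographics that Statistical Analysis intends as a check on randomisation, which would partly measure this selection;
- the between-group difference that the Sample Size paragraph wants to carry into the full-scale trial.

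Specific Aims calls Heard and Understood the primary outcome of Aim 2, so the affected measure is not a peripheral one.

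**Working it through.** **Tracing each step by arm.**

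| Step (section) | Intervention patients | Control patients |
|---|---|---|
| EHR review (Subject Selection) | Defined, before any conversation | Not named |
| Track-board pre-screening (Subject Enrollment) | Defined | Arm not named; could apply |
| Eligibility check with clinician (Subject Selection) | Defined | Not named |
| Approach (Subject Selection) | After completed TLT conversation | No trigger |
| Consent (Subject Enrollment) | After completed TLT conversation | No trigger |
| Capacity (Subject Enrollment) | Clinician who held the conversation | No assessor |
| Heard and Understood; quality of communication (Table 2, no asterisk) | Straight after the conversation | No time defined |
| Decisional regret (Table 2, no asterisk) | 24 h, 48 h, 1 week; origin not stated | Same, origin not stated |
| EHR clinical outcomes (Table 2, no asterisk) | Discharge or death | Same; chart selection not described |
| Acceptability (Table 2, asterisk) | Straight after the conversation | Not due |

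Control clinicians receive neither the TLT training nor the guide (Study Procedures, Control Group), so the conversation-based triggers do not arise for their patients.

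**The protocol's own figures.** The sample size of 32 is 2 × 16, and 16 lies in the cited range of 15 to 20. It reproduces, but it does not bear on this point. Study Termination gives about 3 to 10 seriously ill ICU admissions per clinician per month and about 10 accrued per interventionist clinician in a year:

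- encounters per clinician-year: 3 × 12 = 36 to 10 × 12 = 120;
- share accrued: 10/36 = 28% down to 10/120 = 8%.

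There is therefore room for selection. The gap is not all selection on completion, since eligibility, consent and the 8 AM to 10 PM screening window also contribute. No accrual figure is given for control clinicians.

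**Illustration of size, on assumed inputs.** Let c be the share of eligible intervention patients who complete the conversation, and d the difference in mean outcome between completers and non-completers, in SD. Neither is in the protocol. Suppose TLT has no effect and controls are unselected. The mean over all eligible patients is c·m₁ + (1 − c)·m₀, so completers exceed it by

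bias = m₁ − [c·m₁ + (1 − c)·m₀] = (1 − c)·d.

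| c | d = 0.25 | d = 0.5 |
|---|---|---|
| 0.9 | 0.1 × 0.25 = 0.025 | 0.1 × 0.5 = 0.05 |
| 0.7 | 0.3 × 0.25 = 0.075 | 0.3 × 0.5 = 0.15 |
| 0.5 | 0.5 × 0.25 = 0.125 | 0.5 × 0.5 = 0.25 |

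The sample size does not enter, so more patients do not reduce the bias. Its sign is that of d, which is unknown. Control respondents must also consent, so selection in that arm could offset or add to it. With an entry point that does not depend on TLT, this component is zero.

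**The case against.** The strongest reply is that control patients are plainly intended and that much of the plan does not depend on a conversation. Several parts of it stand.

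- A reader might infer that patients are identified only through a completed conversation. They are not: EHR review and track-board screening come first, and the track-board sentence names no arm. The eligibility text "who are willing to be randomized to become the study interventionists" might even be read as letting the word interventionist cover every enrolled clinician. That would repair screening but not approach or consent, which still need the conversation.
- A reader might infer that control patients have no route into the study at all. The study design section foresees EHR review in both arms. What is missing is how those charts are selected.
- A reader might infer that every outcome is timed to the conversation. Among outcomes due in both arms, only two surveys are. EHR outcomes run to discharge or death, and regret merely lacks a stated origin.
- A reader might infer that the intervention arm holds only patients well enough to talk. Table 1 lets a surrogate take part, which weakens selection on health. Selection on the conversation having taken place remains.
- A reader might infer that every planned between-arm result is confounded. Statistical Analysis names within-arm tests for outcomes, and its one explicit between-arm comparison is of demographics. It also restates the Aim 2 hypothesis without the comparison.

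The last reply does not dispose of the matter. Specific Aims keeps the comparative hypothesis, and the Sample Size paragraph expects a between-group difference from this pilot. Nor does pilot status help: the stated purpose is to show that a randomised design is feasible, and enrolling control patients is part of that.

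**Conclusion.** The point holds as an internal contradiction with a consequence for validity. Followed as written, the protocol requires survey data from control patients but gives them no consent step, capacity assessor or time for the two immediate surveys. It enrols intervention patients only after they have received the intervention. Any between-arm estimate from the unstarred surveys, the demographic check and the difference carried into the full-scale trial would therefore not follow the clinician randomisation.

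The starred acceptability item is rightly restricted to the intervention arm. EHR outcomes are affected only through how charts are selected in each arm.

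The documents do not support a stated size. The 0.025 to 0.25 SD above rests on assumed completion, an assumed completer difference and unselected controls, and shows only that the bias could range from trivial to material. It should be corrected before enrolment, because immediate surveys that were never offered cannot be recovered later.

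**What to change.** Define one entry point for both arms that does not depend on TLT: the first confirmation, from the track board and before any TLT conversation, that a patient of any enrolled clinician meets inclusion a, b or c. Using the ICU admission decision alone would be weaker. The conversation guide covers the decision to try intensive care, so TLT could influence it, and criterion c does not mention ICU admission.

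From that entry point:

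- log all such patients in both arms;
- approach for consent at the same point in the ED stay whether or not a TLT conversation took place, and name who assesses capacity in each arm;
- time Heard and Understood and quality of communication to a common point, such as before leaving the ED;
- start the decisional-regret clock at the common entry point;
- keep the starred item for patients who had the conversation;
- analyse the unstarred outcomes by the clinician's assigned arm.

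Reconcile the study design section, Subject Selection, Subject Enrollment and Table 2 with Outcome Assessments, including which Aim 2 outcomes the control arm supplies.

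The cost is a protocol amendment and research-assistant time to screen and survey control clinicians' patients, which Outcome Assessments already implies. Intervention-arm scores on the unstarred surveys may look less favourable once patients without a TLT conversation are included.

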Experts agree that serious illness care should focus on preparing people for and then supporting them in in-the-moment decision-making during clinical deterioration.^14-16^ Medical crises exemplify the most challenging, in-the-moment decision-making. During medical crises, **time-limited trials (TLT)** are a recommended approach to reducing potentially nonbeneficial treatments for seriously ill older adults.^17-19^ TLT is a structured conversation between clinicians and patients/surrogates to discuss patients’ values and preferences, prognosis, and shared decision-making to use specific therapies for a prespecified period of time. TLT allows both clinicians and patients/surrogates to regularly assess if therapies are meeting patients’ goals over structured time intervals. Guided by the Capacity, Opportunity, Motivation to perform a Behavior (COM-B) framework,^20^ a quality improvement study of TLT in the ICU (N=209) was associated with a 35% increase in formal family meetings (p<0.01), 45% increase in clinicians eliciting values and preferences of patients (p<0.01), 1.3 day decrease in median ICU length of stay (p<0.02), and 13% decrease in mechanical ventilation (p=0.02). No change in hospital mortality was observed (58.4% vs. 58.3%, p=0.99).^21, 22^ TLTs have been published as an expert recommended approach in the official journal of the American College of Emergency Medicine.^23^ Although decisions to initiate intensive care occur in the ED, no study has evaluated the effect of TLT initiated in the ED.

The objective is to assess the feasibility and acceptability of TLT initiated in the ED. We will conduct a pilot randomized trial of TLT on seriously ill older adults starting intensive care in the ED. Rationale: Initiating TLT at the first moment of starting intensive care in the ED may further improve patient-centered outcome compare to the usual care (no TLT). Our central hypothesis is that TLT can be successfully initiated in a randomized study design in the ED.

**Impact:** We anticipate that introduction of TLT in the ED will lead to improved patient-centered utilization of intensive care for seriously ill older adult. If TLT is found to be feasible and acceptable in the ED, the potential exists to standardize the most challenging, in-the-moment decision-making for seriously ill older adults to improve their quality of end-of-life care nationally.

1. **SPECIFIC AIMS AND OBJECTIVES**

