**Aim 2: Determine the patient-reported acceptability of TLT in the ED.**

Hypothesis: The patients and surrogates undergoing TLT conversations will feel heard and understood about their end-of-life care wishes (primary acceptability outcome).

Descriptive statistics will be used for baseline characteristics of the study sample. We will compare patient demographics between study arms to assess randomization using two sample t-test or Wilcoxon rank sum test for continuous variables and chi-square for categorical variables. Within arms, we will use a one-sample binomial exact test of proportions for categorical outcomes (e.g., EHR documentation), and Wilcoxon signed ranks test for ordinal outcomes (e.g., Heard and Understood survey). A significance level, alpha, is set to 0.05. We will conduct a secondary analysis using linear mixed models at baseline and one month to include all non-missing data. The EHR-based outcome will be assessed using an EHR review. We will publish our findings regardless of the results and will follow the CONSORT guidelines for reporting RCT.^43^

**Sample Size:** No previous two-arm trial of TLT has been conducted; thus, the effect size remains unknown. Given the primary purpose of conducting a RCT is to demonstrate the feasibility of conducting a randomized design study, no gold standard for sample size calculations exists. However, prior literature suggest that 15 to 20 participants per group are required to ensure scientific validity of the pilot study results.^44^ Therefore, the present study will include a total of 32 participants with 16 participants per group. In addition, the results of this pilot study will provide information on the difference between groups and standard deviation necessary for sample size calculation during the future full-scale study.

1. **MONITORING AND QUALITY ASSURANCE**

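### The two-arm inpatient EHR documentation outcome includes mention of TLT, an item tied to allocation that can raise the intervention proportion with no change in the other items

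*Protocol*

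**What the plan says.** In the Protocol, Study Procedures, Outcome Assessments, the Aim 1 outcomes come from the intervention arm, with one exception: the "EHR outcome from both intervention and control arms". Table 2 agrees, since EHR documentation by inpatient clinicians is the only Aim 1 row without an asterisk. That row is defined as "Review EHR for new documentation of reference to TLT, serious illness conversation, change in code status, or advance directive forms by inpatient clinicians", assessed at 24 hours, 48 hours and one week.

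Under Intervention in the same section, one component is a template for recording the TLT conversation in the EHR. Another is the handoff to the ICU: "A standard template to communicate the TLT conversation findings to the intensivists has been developed (Appendix". For the control arm: "Emergency clinicians assigned to the control group will not receive the TLT training/guide", and also "No restrictions will be placed on serious illness conversations in the control group". Background and Significance describes the comparator in the phrase "compare to the usual care (no TLT".

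Statistical Analysis, Aim 2, names this analysis: "Within arms, we will use a one-sample binomial exact test of proportions for categorical outcomes (e.g., EHR documentation". The Sample Size paragraph adds that the pilot will supply the between-group difference needed to size a full-scale trial. It does not say for which outcome.

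**The concern.** A two-arm outcome should be able to occur in either arm by the same routes. Three of the four listed items meet that condition. The fourth, a mention of TLT, names the intervention. Only the intervention arm has a built-in channel that puts the term in front of the clinicians whose notes are then searched. An inpatient note that does no more than acknowledge the ED handoff can therefore count as an event.

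At stake is how the two proportions are read side by side. A higher figure in the intervention arm could be taken as a change in inpatient practice when part or all of it is the handoff being repeated. If such a difference were used to plan the full-scale study, the assumed effect would be too large and that trial too small.

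**Working it through.** **Is one yes/no value per patient the intended score?** The Protocol does not say so outright. Three features point that way: the list is joined by *or*; the Outcome Assessments text and both Statistical Analysis subsections speak of the EHR outcome in the singular; and the named test is a one-sample exact binomial test, which needs one binary value per patient.

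**Is there a figure to reproduce?** No. The Protocol gives no expected rate, effect size or power for this outcome. Every rate below is an assumption.

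**Inputs (assumed)**
- p = proportion with at least one of the other three items, equal in both arms (no true effect): 30%.
- r = proportion of intervention patients whose inpatient notes mention TLT: 20%, 50%, 80%.
- c = the same proportion in controls: 0 at first, then 10%.

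**Case 1: mention of TLT independent of the other items.**
The any-of rate is 1 − (1 − p)(1 − r) in the intervention arm and 1 − (1 − p)(1 − c) in control. The difference is (1 − p)(r − c).

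**Case 2: full overlap**, where the smaller group of patients lies wholly inside the larger.
The any-of rate is max(p, r) in the intervention arm and max(p, c) in control.

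With p = 30% and c = 0, the control rate is 30% throughout:

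| r | Case 1: intervention rate | Case 1: difference | Case 2: intervention rate | Case 2: difference |
|---|---|---|---|---|
| 20% | 1 − 0.7 × 0.8 = 44% | 14 points | 30% | 0 points |
| 50% | 1 − 0.7 × 0.5 = 65% | 35 points | 50% | 20 points |
| 80% | 1 − 0.7 × 0.2 = 86% | 56 points | 80% | 50 points |

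**Control notes that mention TLT.** With c = 10%, Case 1 gives 0.7 × 0.1 = 7, 0.7 × 0.4 = 28 and 0.7 × 0.7 = 49 points. In Case 2 nothing changes, because those control patients already count through another item; the difference shrinks only once c exceeds p.

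**Other base rates.** Under independence, with p from 20% to 60% and r from 30% to 80%, the difference runs from 0.4 × 0.3 = 12 points to 0.8 × 0.8 = 64 points when c = 0. It runs from 0.4 × 0.2 = 8 to 0.8 × 0.7 = 56 points when c = 10%.

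**Without the TLT item.** Both arms have rate p, so the difference is 0 whatever r and c are.

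**The case against.** The strongest reply is that the Protocol fixes neither any-of scoring nor a between-arm test for this outcome. The table row can be read as a search instruction to the abstractor, with scoring left to an analysis plan that is not shown. The only named test is within arms. This largely stands. A reader might infer that the Protocol defines a composite and compares it between arms, but neither step is written down. What remains is that the wording favours a single binary outcome, that control data serve little purpose unless set beside the intervention data, and that the pilot is meant to supply group differences.

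A reader might also infer that only the intervention can produce a mention of TLT, so that controls can never score on it. The documents do not support this. The guide was "Originally used in ICU settings", intensivists are not randomized, and nothing bars them from starting and recording a time-limited trial for a control patient. The supportable claim is that the item is more likely in the intervention arm.

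Nor does the item measure only delivery of the intervention. The entry must be new and written by an inpatient clinician, so the ED note itself does not count, and delivery is already observed with the fidelity checklist. Whether the ICU team takes up the ED plan is a legitimate feasibility question. That is a reason to keep the item and report it separately, not a reason to pool it with the other three.

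Finally, independence is doubtful, because a note that cites a time-limited trial may well also record a conversation or a code status change. That is why the full-overlap case is shown; at a low echo rate it removes the artefact.

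**Conclusion.** The point holds in a limited form. The two-arm outcome contains one item linked to allocation through the handoff template. Scored as any-of, it raises the intervention proportion relative to control without any change in the three arm-neutral items, unless every patient whose note mentions TLT already counts through another item. The direction follows from r exceeding c. The size cannot be known from the Protocol: at an assumed 30% base rate, with r from 20% to 80% and no control mentions, it is 14 to 56 points under independence and 0 to 50 under full overlap. These figures show what pooling could do and are not estimates for this trial.

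The consequence is moderate. The outcome is secondary, and none of the three feasibility thresholds in Statistical Analysis, Aim 1, uses it. The change is still worth making, because the definition and the arms of collection are set in the Protocol itself.

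**What to change.** 1. In Table 2, limit the two-arm outcome to new inpatient documentation of a serious illness conversation, a change in code status or an advance directive form.
2. Report mention of TLT as a separate item, still abstracted in both arms: as uptake in the intervention arm and as contamination in the control arm. Do not mark it with an asterisk, since that would discard the control-arm mentions that show contamination.
3. State in the abstraction rules that a note which only restates the ED TLT handoff does not count as a new serious illness conversation. Otherwise the same artefact returns through the second item.

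The cost is a small edit to one row of Table 2 and to the abstraction form. The chart review is the same and no new data are needed.
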